### Aims

The project aims to evaluate G4H in comparison to the current gold standard evidence-based psychological treatment for youth depression, CBT. Based on the existing evidence, we predict:*Hypothesis 1:* At program completion, G4H will be superior to CBT in reducing loneliness (a major risk factor for relapse in depression).*Hypothesis 2:* At program completion, G4H will be as effective as CBT in reducing symptoms of depression (i.e., be non-inferior)*Hypothesis 3:* The benefits of G4H for loneliness and depression will be sustained at 12-month follow up.

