## Method

### Trial design

CARR is a two-arm non-inferiority parallel (1:1 ratio) randomised controlled trial. A summary of this study’s compliance with Standard Protocol Items: Recommendations for Interventional Trials (SPIRIT), is provided in the Additional file 1.

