### Sample size power calculations

The CARR sample size was determined by power calculations for a non-inferiority trial, using effect sizes and retention rates from our published pilot study. We have estimated the non-inferiority margin based on historical evidence for the effect size of the active comparator (based on recommendations by [46] and [47]). The effect size of this CBT program versus control was *d* = 0.49 at 6 month follow up (recalculated from [28] using methods recommended by [19]). This corresponds to 2.2 points on the DASS-21 depression subscale (using the expected standard deviation for an adolescent population of 4.53; [31]). To have 0.80 power to detect this difference with an alpha level of 0.05*,* 67 people per condition would need to be retained at follow up. Assuming 50% eligibility and 67% survival rates, which are consistent with our pilot data, we anticipate that screening 400 people for eligibility (see Fig. 2) will lead to retention of *N* = 67 per condition at follow up [48]. However, this is a conservative estimate of retention due to the addition of incentives for follow up data completion in this trial [49].

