H1 will be considered supported if there is evidence of significant improvements in loneliness in the G4H condition (H1a), and a significant condition by time interaction, such that improvements in loneliness over time will be greater for the G4H condition than in the CBT condition (H1b). H2 will be considered supported if there is evidence of significant improvements in depression in both conditions, with a non-significant condition by time interaction. The non-inferiority margin will be a DASS-21 depression change score difference of 2.20. H3 will be considered supported if there is no significant increase in depression and loneliness scores between T6 and T7 in the G4H condition.

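### H2 (non-inferiority on depression) is decided by a non-significant interaction and is not tied to the 2.20 margin, so a deficit of the full margin can pass and a superior G4H can fail

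*Protocol article*

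**What the plan says.** Under Aims, the protocol article words Hypothesis 2 as: "At program completion, G4H will be as effective as CBT in reducing symptoms of depression (i.e., be non-inferior"). Trial design confirms the framework: "CARR is a two-arm non-inferiority parallel (1:1 ratio) randomised controlled trial". The sample size section says the same: "The CARR sample size was determined by power calculations for a non-inferiority trial".

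The decision rule is in the Analyses section: "H2 will be considered supported if there is evidence of significant improvements in depression in both conditions, with a non-significant condition by time interaction". The next sentence gives the margin: "The non-inferiority margin will be a DASS-21 depression change score difference of 2.20". The text then moves on to H3. It does not say which estimate or limit is compared with 2.20, and the article mentions no confidence interval, bound or one-sided test.

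The margin comes from the effect of this CBT program against control, d = "0.49 at 6 month follow up". On the conversion to points, the article says: "This corresponds to 2.2 points on the DASS-21 depression subscale".

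**The concern.** A non-inferiority claim needs evidence that a deficit as large as the margin can be excluded. The stated rule asks whether a test of no difference failed to reject, and that can happen because the arms are similar or because the estimate is imprecise.

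There are two consequences.

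- **False support.** H2 can be declared supported while the data remain compatible with G4H being worse by 2.20 or more. On the protocol's own derivation, 2.20 is the whole benefit of this CBT program over control, so this is a serious deficit to let through.
- **False failure.** The interaction criterion for H2 has no direction, unlike the one for H1b. A G4H that is significantly better than CBT on depression produces a significant interaction, and H2 is then formally not supported.

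**Working it through.** **Inputs.** From the sample size section: SD 4.53, margin 2.2 points, power 0.80, alpha 0.05 (sidedness not stated), 67 retained per arm. From Analyses: margin 2.20 and the H2 rule. The SD is taken as that of the change score, since the protocol's own calculation uses it for the compared quantity. The interaction is represented by a two-sample t test of change at one timepoint.

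**1. The plan's own figure.** 0.49 × 4.53 = 2.22, stated as 2.2. For a non-inferiority comparison with zero true difference and one-sided 0.025:

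n = 2 × (1.960 + 0.842)² × 4.53² / 2.20² = 66.6, so 67 per arm.

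The stated 67 reproduces. One-sided 0.05 would give 53, which does not match. Retention also agrees: 400 × 0.50 × 0.67 / 2 = 67.

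**2. What each rule accepts.** SE = 4.53 × √(2/67) = 0.783. The critical t on 132 df is 1.978, so the half-width is 1.978 × 0.783 = 1.55. Write the difference as G4H minus CBT, positive when G4H is worse.

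- Interaction non-significant: observed difference between −1.55 and +1.55.
- Upper 95% limit below 2.20: observed difference below 2.20 − 1.55 = 0.65.

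Observed deficits from about 0.65 to 1.55 therefore satisfy the interaction criterion although the interval includes the margin. For example, an observed deficit of 1.50 has an upper limit of 1.50 + 1.55 = 3.05.

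**3. True deficit of 2.20.** The interaction is non-significant with probability 20.3% (noncentral t). The written rule also requires significant improvement in both arms. The protocol gives no expected improvement, so I assumed a range and simulated the full rule at 67 per arm:

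| Assumed true CBT improvement (points) | P(H2 supported), written rule | 95% confidence-limit rule |
|---|---|---|
| 2.2 | 2% | 2.5% |
| 2.5 | 5% | 2.5% |
| 3.0 | 14% | 2.5% |
| 3.5 | 19% | 2.5% |
| 4.0 or more | 20% | 2.5% |

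**4. G4H truly better by 2.20.** By symmetry the interaction is non-significant 20.3% of the time, so H2 fails about 80% of the time. The confidence-limit rule supports non-inferiority more than 99.9% of the time.

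**5. Less information (assumed values, illustration only).** With a true deficit of 2.20 and 50 per arm, the full written rule gives false support of 16% if CBT improves by 3.0 points and 33% if it improves by 5. With 67 per arm and a design effect of 1.3 to 1.6 for therapy groups, it is about 16% at an improvement of 3.0 and 31% to 40% at 5. The confidence-limit rule stays at 2.5% throughout.

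**The case against.** The strongest defence is that the margin directly follows the H2 criterion and the trial is sized on it, so the authors may have meant it to apply, with the mechanics left to an analysis plan that is not shown. This stands in part. A reader might infer that the plan has no margin, and that would be wrong. But the article does state when H2 counts as supported, and that condition does not refer to the margin. If the margin was meant as an added condition, false support would be controlled, but a superior G4H would still fail because the interaction must be non-significant.

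Second, the requirement that both arms improve does give protection. A reader might infer that false support is always 20%, or simply equals the type II error of a superiority test. The table shows otherwise: 20% is a ceiling, reached only if CBT improves by roughly 3.5 points or more. Nor can regression to the mean be assumed to satisfy the requirement. Entry is by PHQ-9, a diagnosis or UCLA loneliness, and none of these selects on DASS-21 depression.

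Third, a reader might count acceptance at a smaller true deficit, such as 1.1 points, as an error. It is not: 1.1 lies inside the margin, so G4H is then non-inferior by the protocol's definition.

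Fourth, the planned analysis is a mixed model over all timepoints with a therapy-group level, so the percentages are illustrative. The 2.5% level is inferred from the reproduced sample size, because the article does not state sidedness.

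Finally, failing H2 when G4H is superior mislabels a hypothesis; it does not create a false efficacy claim, and the advantage would be visible in the same analysis. This limb is real but secondary.

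**Conclusion.** The point holds. The stated H2 criterion does not test non-inferiority, and the 2.20 margin is not tied to the decision. This is a rule stated wrongly in the article, not a detail deferred to an analysis plan.

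At 67 per arm, a G4H worse by the full margin would be declared non-inferior between about 2% and 20% of the time, against 2.5% under a confidence-limit rule. A G4H better by 2.20 would fail H2 about 80% of the time. These sizes rest on SD 4.53 as the change-score SD, independent observations, a single-timepoint comparison and assumed CBT improvements.

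A reader might infer that smaller samples always make false support more likely. The documents do not support that without a condition. The upper value rises as information falls, but only if within-arm improvement is large enough to remain significant in both arms. The sample sizes and design effects used to show this are assumptions.

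**What to change.** Replace the H2 criterion with wording such as: H2 is supported if the upper limit of the two-sided 95% confidence interval for the G4H minus CBT difference in DASS-21 depression change from T0 to T5, estimated from the planned mixed model, lies below 2.20 in both the ITT and per-protocol analyses; if the whole interval lies below 0, superiority may be claimed. Remove the non-significant interaction as a criterion. Significant improvement within each arm can still be reported descriptively.

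The cost is one sentence. The model, the data and both analysis sets are already planned. The stated 67 per arm gives 80% power for this rule at zero true difference and one-sided 0.025, on the protocol's own assumption of independent observations. This change therefore needs no extra participants. Whether 67 is enough once therapy-group clustering is allowed for is a separate question.

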**Methods:**

The CARR trial is a two-arm non-inferiority randomised controlled trial that will compare the efficacy of G4H to the most widely used evidence-based treatment for depression, CBT, at program completion and 6- and 12-month follow up. Participants will be 200 young people (aged 15–25) with symptoms of depression and/or loneliness recruited from community and university mental health services. We hypothesise that the interventions will be comparable in reducing depression symptoms, but that G4H will be superior in reducing loneliness. Because loneliness is a primary risk factor for depression relapse in young people, we therefore expect the benefits of Groups 4 Health to be particularly apparent at 12-month follow up.

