### Measures

Each participant will be asked to complete online surveys (or paper-and-pencil if they prefer) at eight time points. The full questionnaire package measuring all outcomes of interest will be administered before the intervention (T0), on its completion (T5), 6 months later (T6) and 12 months later (T7) – see Table 1 for a summary. These should take about 10–20 min on each occasion. In addition, a brief one-page questionnaire will be administered at the end of each session (T1, T2, T3, and T4), which will (only) include measures of depression symptoms, loneliness, module feedback, and group identification.

**Table 1 Tab1:** Overview of CARR measures and timepoints of measurement

Construct	Measure	T0 Baseline	T1 After session 1	T2 After session 2	T3 After session 3	T4 After session 4	T5 Post-treatment	T6 6-month follow up	T7 12-month follow up
Primary outcomes	Depression (DASS-21)	•	•	•	•	•	•	•	•
	Depression (PHQ-9)	•					•	•	•
	Loneliness (4 item)	•	•	•	•	•	•	•	•
	Loneliness (20 item)	•					•	•	•
Secondary outcomes	Social anxiety	•					•	•	•
	GP attendance (last month)	•					•	•	•
	Wellbeing	•					•	•	•
	Life satisfaction	•					•	•	•
	Self esteem	•					•	•	•
	Subjective physical health	•					•	•	•
Process measures	Multiple group membership	•					•	•	•
	Multiple group compatibility	•					•	•	•
	Mental illness identity	•					•	•	•
	Group cohesion						•		
	Therapy group identification		•	•	•	•	•		
	Service identification						•		
Acceptability/feasibility	Useful		•	•	•	•	•	•	•
	Enjoyed						•	•	•
	Interesting						•	•	•
	Learnt something						•	•	•
	Homework completion		•	•	•	•	•		
	Facilitator questionnaire		•	•	•	•	•		
	Attendance		•	•	•	•	•		

Notes: *DASS21* Depression Anxiety Stress Scales (21 item)

*PHQ-9* Patient Health Questionnaire (9 item).

*GP* General Practitioner

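### The H3 rule tests only months 6 to 12 and accepts a non-significant rise, so a benefit lost between program completion and month 6 would still be declared sustained

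*Protocol article*

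**What the plan says.** In the protocol article, Aims, H1 and H2 are both framed at program completion, and H3 reads "The benefits of G4H for loneliness and depression will be sustained at 12-month follow up". Under Measures, the full questionnaire is given "before the intervention (T0), on its completion (T5), 6 months later (T6) and 12 months later (T7"), so program completion is T5.

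The Analyses section then fixes the test: "H3 will be considered supported if there is no significant increase in depression and loneliness scores between T6 and T7 in the G4H condition". The rule has no contrast that involves T5 or T0, and no limit on the size of rise that still counts as sustained. The only margin in the document, 2.20 points, belongs to the depression comparison under H2.

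Separately, the Methods part of the abstract says that the authors "expect the benefits of Groups 4 Health to be particularly apparent at 12-month follow up".

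**The concern.** The hypothesis and its test cover different intervals. The benefit to be sustained exists at T5, but the test takes T6 as its starting point, so any loss in the first six months after treatment lies outside it.

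The rule also treats failure to find a rise as evidence that none occurred. With no tolerance set, an imprecise estimate passes as readily as a precise one near zero.

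Relapse reduction is in the trial's title, and the Discussion offers the program as an approach to relapse prevention. H3 is the hypothesis that speaks to durability, so a rule that can confirm it after the benefit has gone would undermine the claim that readers care about most.

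**Working it through.** **Inputs from the document**
- Effect of the CBT program versus control: d = "0.49 at 6 month follow up" (Sample size power calculations).
- "This corresponds to 2.2 points on the DASS-21 depression subscale", "using the expected standard deviation for an adolescent population of 4.53" (same section).
- "To have 0.80 power to detect this difference with an alpha level of 0.05", with 67 per condition retained (same section). Sidedness is not stated.
- Pilot retention: of 81 people, 54 completed the program and 26 completed the 6-month follow-up (Background, Groups 4 health).

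**Assumption not in the document:** the within-person correlation ρ between two follow-up scores, taken as 0.5 with a range of 0.3 to 0.7.

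**Step 1. Reproduce the plan's own figure.** 0.49 × 4.53 = 2.22, stated as 2.2. With two-sided 0.05 and the normal approximation, n per arm = 2 × 4.53² × (1.96 + 0.8416)² / 2.2² = 66.6, so 67. The stated figure reproduces and is not in dispute. It is a two-arm calculation and does not cover H3.

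**Step 2. Benefit lost before T6, then flat.** The true T6-to-T7 change is zero. A two-sided 0.05 test finds a significant increase with probability 0.025, so each outcome passes with probability 1 − 0.025 = 0.975. This depends on neither n, SD nor ρ. Both outcomes pass together at least 1 − 2 × 0.025 = 95% of the time.

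**Step 3. True worsening between T6 and T7, depression only.** Paired t-test in one arm:
- SD of change = 4.53 × √(2(1 − ρ)), which is 5.36, 4.53 and 3.51 for ρ = 0.3, 0.5 and 0.7.
- Noncentrality = rise / (SD of change / √n). For a 2.2-point rise at ρ = 0.5 this is 2.2 / 0.553 = 3.98 with n = 67, and 2.2 / 0.801 = 2.75 with n = 32.
- P(pass) = P(noncentral t below the upper 2.5% point of t on n − 1 df).

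The case n = 32 applies the pilot's 6-month rate, 26/81 = 32%, to 100 per arm. The planned 67% equals the pilot's program-completion rate, 54/81.

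| True rise T6 to T7 | n = 67: ρ 0.5 (ρ 0.7 to 0.3) | n = 32: ρ 0.5 (ρ 0.7 to 0.3) |
|---|---|---|
| 0 | 97.5% | 97.5% |
| 1.1 | 50% (28% to 62%) | 74% (60% to 80%) |
| 2.2 | 2.5% (0.1% to 9%) | 24% (7% to 39%) |

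**Step 4. A confidence-limit rule, for comparison.** Pass if the upper limit of the 95% interval for the T5-to-T7 change lies below a tolerance. With 2.2 used purely for illustration, a true rise of 2.2 passes 2.5% of the time at any n. True maintenance passes 97.5% (91% to 99.9%) at n = 67 and 76% (61% to 93%) at n = 32. Dropout now counts against the claim.

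**The case against.** **The trial would see an early loss.** This stands. Depression and loneliness are measured at T5, T6 and T7 in both arms, and Analyses puts all available timepoints in the mixed model. A reader might infer that relapse before month 6 is invisible altogether, but it is invisible only to the H3 verdict.

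**Dropout does not always help.** This also stands. A reader might infer that high dropout makes success more likely in general. That holds only if scores truly worsen after T6. With flat scores the pass rate is 97.5% at any n.

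**At the planned size the rule catches large rises.** With 67 retained, a 2.2-point rise passes only 2.5% of the time (at most 9%). The 50% pass rate for a 1.1-point rise is not good evidence against the rule, because a 2.2-point confidence limit passes the same rise 49.9% of the time at that n and correlation.

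**The case with 32 is pessimistic.** The protocol adds payments for each follow-up and calls its retention estimate conservative for that reason. The mixed model would also recover some partial data, although clustering by therapy group pushes the other way.

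**H3 makes no claim against CBT.** A reader might infer from the abstract's 12-month expectation that H3 must be tested against CBT. H3 as worded in Aims concerns the benefits of G4H, and the abstract sentence is not one of the numbered hypotheses. The missing comparison is therefore not an error in the H3 rule.

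None of this answers the central point: the rule starts six months after the benefit that it is meant to protect, and it has no tolerance.

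**Conclusion.** The H3 rule is wrong as written. The protocol fixes it, so it is not a detail left to an analysis plan, and it does not test H3 as stated in Aims.

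The main defect is the interval: complete loss between T5 and T6 followed by flat scores passes about 97.5% of the time per outcome. That figure rests only on a two-sided 0.05 test.

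The second defect is reading non-significance as maintenance. Its size depends on retention: a 2.2-point rise after T6 passes 2.5% (0.1% to 9%) with 67 in the arm and 24% (7% to 39%) with 32. These figures assume complete pairs, SD 4.53 and ρ of 0.3 to 0.7. They cover depression alone and are upper bounds for H3 as a whole, since loneliness must pass too. No loneliness SD is given, so that outcome was not computed. The verdicts on H1 and H2 do not depend on this rule.

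**What to change.** In the existing mixed model, base H3 on the T5-to-T7 change in the G4H arm. Declare it supported only if the upper 95% confidence limit lies below a prespecified tolerance for each of depression and loneliness.

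The sponsor must set and justify both tolerances. The 2.20 margin is a between-arm figure equal to the whole assumed CBT effect, so for a within-arm change in depression it is at most an upper bound. The document gives no figure for loneliness.

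Report the G4H minus CBT contrast at T7 (change from T0) with its 95% confidence interval as supporting evidence, not as part of the H3 criterion.

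**Cost.** No new data are needed, but choosing the tolerances takes real work and is more than a change of wording. H3 becomes harder to declare, especially with high dropout: even at a limit of 2.2 and ρ = 0.5, true maintenance passes about 97.5% of the time with 67 in the arm but 76% with 32. A tighter tolerance would lower both.

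### H3 claims that the gain at program completion lasts to 12 months, but its rule tests only T6 to T7, so a gain lost in the first six months still counts as sustained

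*Protocol article*

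**What the plan says.** In the Aims section of the protocol article, H1 and H2 are both tied to the end of the program: "At program completion, G4H will be superior to CBT in reducing loneliness" and "At program completion, G4H will be as effective as CBT in reducing symptoms of depression". H3 then follows: "The benefits of G4H for loneliness and depression will be sustained at 12-month follow up".

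The Measures section fixes the labels. The full questionnaire is given at baseline (T0), "on its completion (T5), 6 months later (T6) and 12 months later (T7"). Table 1 and the Primary outcomes section show DASS-21 depression and the 20-item UCLA scale collected at T0, T5, T6 and T7.

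The Analyses section puts all available timepoints into the mixed model and then gives a success rule for each hypothesis. For H3 it is: "H3 will be considered supported if there is no significant increase in depression and loneliness scores between T6 and T7 in the G4H condition". The rule names no other timepoint and does not refer to H1 or H2.

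**The concern.** The hypothesis and its rule cover different periods. The benefits in question are those present at T5, so to sustain them to 12 months means that they are still there at T7. The rule compares T7 with T6, a point already six months after completion. What happens between T5 and T6 does not enter it.

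H3 is the only one of the three rules that asks whether G4H keeps its own gain, and durability is central to a trial named for reducing relapse. A report that H3 was supported would be read as evidence of lasting benefit. Under the rule as written, that report is equally likely whether the gain was kept in full or lost in full before T6.

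This is a stated success criterion with named timepoints, not a detail left to an analysis plan. An analysis plan that followed it would inherit the mismatch.

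**Working it through.** **Inputs from the protocol article (Sample size power calculations):** SD of DASS-21 depression 4.53; difference 2.2 points; power 0.80; alpha 0.05; 67 retained per arm; 400 screened, 50% eligible, 67% retained.

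**Assumptions not in the document:** two-sided 0.05 tests; within-person correlation ρ of 0.5 (also 0.3 and 0.7); paired t-tests in place of the MMRM; no therapy-group clustering; H3 fails if either outcome rises significantly.

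**1. The plan's own figure.** n per arm = 2 × (1.96 + 0.8416)² × 4.53² / 2.2² = 2 × 7.849 × 20.52 / 4.84 = 66.6, rounded up to 67. Attrition: 400 × 0.5 × 0.67 / 2 = 67. Both reproduce. The H3 rule has no figure of its own.

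**2. The logic.** Write the G4H means as m0, m5, m6, m7. The claim concerns m7 − m5, which equals (m6 − m5) + (m7 − m6). The rule tests only m7 − m6. The first term can take any value without changing the outcome of the rule.

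**3. All loss before T6.** If m7 = m6, a two-sided 0.05 test shows a significant rise with probability 0.025, so one outcome passes with probability 0.975, whatever the SD or ρ. For both outcomes I used 10,000 simulated trials of 67 participants, with an illustrative gain of 0.49 SD by T5 on each outcome, correlation 0.5 between outcomes, and ρ of 0.3, 0.5 and 0.7:

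| True course in G4H | T6–T7 rule: supported | Same rule started at T5 |
|---|---|---|
| Gain fully kept | 0.954–0.956 | 0.955–0.957 |
| Gain wholly lost by T6, then flat | 0.955–0.957 | 0.024 / 0.005 / 0.000 (ρ 0.3 / 0.5 / 0.7) |
| No improvement at any time | 0.952–0.955 | 0.952–0.957 |

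The written rule gives the same answer in all three rows. Starting at T5 separates the second row from the first but not the third, which needs a comparison with T0.

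**4. Loss spread over the year.** Take a rise of 1 point in each half-year, 2 points in all. SD of a change = 4.53 × √(2(1 − ρ)) = 4.53 at ρ = 0.5, and its standard error is 4.53/√67 = 0.553.

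- T6–T7 rule, depression alone: noncentrality 1/0.553 = 1.81 on 66 df; probability of a significant rise 0.429; passes 0.571.
- T6–T7 rule, both outcomes, with the same standardised rise in loneliness: about 0.32 to 0.45 as the correlation between the two change scores goes from 0 to 0.7.
- T5–T7 contrast, depression alone: noncentrality 2/0.553 = 3.61; detects the loss with probability 0.945. At ρ = 0.3 the SD of change is 5.36, the standard error 0.655, the noncentrality 3.05 and the probability 0.853.

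**The case against.** The strongest reply is that the rest of the plan would reveal a failure. Three parts of it deserve weight.

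*No improvement at all.* A reader might infer that G4H could do nothing and the trial would still claim sustained benefit. The documents do not support that as a main charge. H1 requires a significant loneliness improvement in G4H (H1a), and for depression "H2 will be considered supported if there is evidence of significant improvements in depression in both conditions". If G4H never improved, both would fail, and few readers would then take H3 as a benefit kept. What stands is narrower: H3 is not formally conditional on either rule.

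*The only 12-month test.* A reader might also infer that nothing else looks at 12 months. That goes too far. The Abstract says the arms are compared at completion, 6 and 12 months, and the Analyses section models all timepoints, so T6 and T7 data are in the comparison of arms and a rebound after T5 would be visible in the fitted means. But an arm-by-time interaction does not test whether G4H keeps its own gain, so this does not repair the H3 rule.

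*The illustration.* The 4.53 is described as an adolescent population SD. With an assumed SD of 6, detection of the 2-point loss by a T5–T7 contrast falls to about 77% (62% at ρ = 0.3). Clustering is ignored too. These points weaken the figures in step 4, not the logic in step 2 or the 0.975 in step 3.

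T6 may be a slip for T5. Nothing in the document says so, and a slip in a success criterion still needs correcting.

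**Conclusion.** The concern holds as a mismatch between the H3 hypothesis and its decision rule. The hypothesis runs from T5 to T7; the rule covers only the second half of that period. A gain lost completely by T6 passes with probability 0.975 per outcome and about 0.95 to 0.96 jointly, no different from a gain fully kept. That result needs only a test at two-sided 0.05 and flat scores after T6; the joint figure varies slightly with the correlation between outcomes.

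For loss spread evenly over the year the rule is weak rather than blind: it passes 57% of the time for depression alone and about 32% to 45% jointly, against about 94% detection of the depression loss from T5. Those figures rest on the stated SD, 67 retained, ρ = 0.5 and no clustering. The missing link to baseline is secondary, because H1a and H2 cover it separately. The sample size is not in question.

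**What to change.** In the Analyses section, restate the H3 rule within the planned MMRM, for DASS-21 depression and UCLA-20 in the G4H arm, as two requirements:

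1. the T7 score is significantly better than the T0 score; and
2. there is no significant increase from T5 to T7, with the estimated change reported with its 95% CI.

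Report T5–T6 and T6–T7 changes descriptively. Both requirements are needed: the second catches early loss, and the first prevents flat scores at baseline level from passing.

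Requirement 2 still reads a non-significant result as maintenance. The CI lets a reader see how much loss remains possible. A formal upper bound on the loss would be a separate decision, and the document gives no such amount for UCLA-20.

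The cost is a change of wording in one rule. All four timepoints are already collected and modelled, so no new data are needed. The downside is that H3 becomes harder to claim.
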